## Abstract

**Background:**

In the treatment of Lateral Epicondylitis (LE) no single intervention concerning injection therapies has been proven to be the most effective with regard to pain reduction. In this trial 3 injection therapies (perforation with application of autologous blood, perforation with application of dextrose and perforation only) will be compared in a standardized and ultrasound guided way. The objective is to assess the effectiveness of these 3 injection therapies on pain, quality of life and functional recovery. By conducting this study, we hope to make a statement on the effectiveness of injection therapy in the treatment of LE. Hereby, unnecessary treatments can be avoided, a more universal method of treatment can be established and the quality of the treatment can be improved.

**Methods/design:**

A multicenter, randomized controlled trial with a superiority design and 12 months follow-up will be conducted in four Dutch hospitals. One hundred sixty five patients will be recruited in the age of 18 to 65 years, with chronic symptomatic lateral epicondylitis lasting longer than 6 weeks, which have concordant pain during physical examination. Patients will be randomized by block randomization to one of the three treatment arms. The treatment will be blinded for patients and outcome assessors. The following three injection therapies are compared: perforation with application of autologous blood, perforation with application of dextrose and perforation only. Injections will be performed ultrasound guided in a standardized and automated way. The primary endpoint is: pain (change in ‘Visual Analogue Scale’). Secondary endpoints are quality of life and functional recovery. These measurements are collected at baseline, 8 weeks, 5 months and 1 year after treatment.

**Discussion:**

When completed, this trial will provide evidence on the effectiveness of injection therapy in the treatment of lateral epicondylitis on pain, quality of life and functional recovery. In current literature proper comparison of the effectiveness of injectables for LE is questionable, due to the lack of standardization of the treatment. This study will overcome bias due to manually performed injection therapy.

**Trial registration:**

This study is registered in the Trial Register (www.trialregister.nl) of the Dutch Cochrane centre. Trial ID; NTR4569. http://www.trialregister.nl/trialreg/admin/rctview.asp?TC=4569

## Background

In the Dutch population seven in 1000 patients visiting a general practitioner (GP) are diagnosed with a lateral epicondylitis (LE) or tennis elbow. The incidence of LE seems independent of sex and ethnical background. Only age influences the incidence with the highest incidence between 40 and 50 years. LE is a disease that is associated with patients in working age from the age of 20 up to 65 [1]. The Dutch Standard on LE for GPs states that about 20% of the patients with LE do not recover within 6 months and 10% not even in 12 months. Each year a GP refers about 2% of the patients with LE to an orthopaedic surgeon [2, 3].

There are several hypotheses regarding the cause of the tendinosis in LE based on histopathological, biochemical and clinical findings. Cell apoptosis, angiofibroblastic features, or abnormal biochemical adaptations, largely suggest that a failed healing response underlies the condition [4, 5]. With respect to the origin more consensus exists, i.e. the Extensor Carpi Radialis Brevis (ECRB) tendon is most commonly affected [6].

Currently, different injectables are used in the treatment of LE without proper scientific evidence [1]. A meta-analysis by Krogh et al. [7] confirmed this statement and found a paucity of evidence from unbiased trials on which to base treatment recommendations for LE. However, this meta-analysis also showed that perforation with application of autologous blood and prolotherapy (injection with dextrose) both seemed more effective than placebo on pain reduction. In addition, these injectables seemed to be more effective after six weeks than corticosteroids on pain reduction.

Autologous blood contains platelets with growth factors that may help in the healing process of chronic injuries. These platelet growth factors stimulate the healing process and lead to partial modification of the damaged tissue. The hypothesis is that these growth factors stimulate angiogenesis and cell proliferation and increase tensile strength and the recruitment of repair cells.

Injection therapy with application of dextrose is a common treatment in chronic musculoskeletal pain, including LE. Animal model studies suggest that the treatment by perforation with application of dextrose may enlarge and strengthen ligament and tendon insertions. The precise mechanism is unclear [8].

Besides the effectiveness of the injectables, the hypothesis is that the needle is used to either break up scars or poke holes in the injured tendon so that bleeding occurs. The blood cells carry precursors, which eventually develop into collagen to replace the damaged tendon. Therefore, this study compares the different injectables with perforation without application of an injectable.

The current debate on studies related to injectables for LE is that in most cases the perforations are performed manually and ‘blindly’ without ultrasound guidance. Moreover, the number and depth of perforations is often not defined. Proper comparison of injectables for LE is therefore questionable [7]. The proposed study compares the effectiveness of perforation of the Extensor Carpi Radialis Brevis (ECRB) tendon to perforation with application of autologous blood or dextrose in the treatment of LE in a standardized and ultra-sound guided way. This overcomes bias due to manually performed injection therapy.

Our hypothesis is that there is no difference in effectiveness between perforation only and perforation with application of one of the injection fluids. The potential health care efficiency gain consists of more homogeneity in the treatment of LE. Hereby, unnecessary treatments can be avoided, a more universal method of treatment can be established and the quality of the treatment can be improved.

The primary objective of this study is to compare the difference in effectiveness of perforation only versus perforation with application of autologous blood or dextrose on pain in the treatment of LE. The primary endpoint is pain on the lateral side of the elbow after a provocation test 5 months after treatment. The secondary objectives are to examine quality of life and functional recovery.

## Methods/design

### Study design

This trial is a multicenter, blinded, three-arm randomized controlled trail with a superiority design with a 12 months follow-up. Data will be presented in line with the CONSORT statement.

### Population

Patients will be recruited in four large teaching hospitals in the Netherlands; Amphia Breda, OLVG Amsterdam, Martini hospital Groningen and Deventer hospital. A total of 165 patients are needed; 55 patients will be included in each of the three trial arms.

#### Inclusion criteria

Patients with chronic symptomatic lateral epicondylitis that have not responded to conservative treatment are eligible to take part when they meet all the following inclusion criteria;Symptoms lasting longer than 6 weeks.Age from 18 to 65 years.Concordant pain during physical examination; pain during palpation of the lateral epicondyle and pain during dorsiflexion of the wrist (from a neutral position and elbow straight) against resistance.Unilateral LE (mild cases of LE on the contralateral elbow without functional limitations are allowed).Able to read and write in Dutch and should provide informed consent.

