### Outcome measures and endpoints

#### Demographic variables

Descriptive data will be reported before treatment (baseline) of all participants regarding age, sex, body mass index, dominant arm, job and whether they smoke or not (by the question; do you smoke?). The jobs of the subjects will be classified according to the International Standard Classification of Occupations (ISCO-08).

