### Recruitment and enrollment

All consecutive patients presenting to the department of orthopedic surgery with LE who meet the inclusion criteria will be invited to participate in the trial. The treating surgeon or resident will introduce the trial to the patient and address the patient’s questions. Information will be handed to the patient to read at home. If the patient is willing to participate, informed consent will be obtained. Participants may take as long as they like to consider participation, provided that they still meet all eligibility criteria.

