To get a better understanding, a linear mixed model analysis will be performed with the three repeated measurements of pain VAS as dependent variables. Along with treatment (a three-level nominal variable) the following covariables will be included in the model as independent variables: baseline pain VAS, the binary variable perceived aggravation of pain due to work ((totally) agree vs otherwise) and a three-level nominal variable time (visit number). Moreover, the interaction between treatment and time will be tested. If this interaction is not significant at the 0.01 level, then one overall treatment effect will be estimated assuming parallelism of the treatment effect. If this interaction turned out to be significant at the 0.01 level, then the effect of the 5 months’ visit will be considered the main effect of interest. Effects will be quantified by estimating two-sided 98% confidence intervals of the pair wise mean differences in pain VAS between the three treatment groups. Equivalence between two treatments is accepted if such a confidence interval is totally overlapped by the interval − 10 + 10. A restricted maximum likelihood estimation method will be used to estimate the coefficients so that missing values are properly imputed in order to meet the itt-condition. Under the pp-condition only patients with non-missing observations will enter the linear mixed model.

Similar analysis will be performed for functional recovery and quality of life. Otherwise the descriptives of the secondary outcome measures will be reported for the three groups.

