There is a paucity of evidence on the effectiveness of all injectables used in the treatment of LE and it is still questionable if there is a major benefit of injection therapies given the self-limiting nature of the condition. [7] Therefore one of the treatment arms in this study does not include an infiltration but is perforation only. It is hypothesized that bleeding occurs in the affected ECRB tendon by poking holes with the needles. This blood cells carry precursors, which eventually could develop into collagen to replace the damaged tendon. No placebo group is included in this study. This has been chosen because of the expected inclusion difficulties. In our experience it is challenging to motivate a patient to participate in a study with a placebo group. Especially when the complaints are disabling and persistent.

For practical reasons, it was chosen not to include all different injectables. Due to the self-limiting character in the majority of cases, the number of participants needed to demonstrate a clinically relevant difference would be too high for feasibility. Ideally, in future studies all different injection therapies should be compared to a placebo or sham injection group. However, we think our study takes the most important injection therapies into account and given the standardized design, this study will be a valuable addition to current literature.

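### Symptom duration at entry is probably prognostic for the 5-month pain score, but it is not in the listed baseline variables, the strata or the mixed model

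*Protocol article*

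**What the plan says.** Inclusion criteria: "Patients with chronic symptomatic lateral epicondylitis that have not responded to conservative treatment are eligible", with "Symptoms lasting longer than 6 weeks" as the only limit on duration. No upper limit is given, and neither the type nor the length of the conservative treatment is stated.

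Background, citing the Dutch general-practice standard: "about 20% of the patients with LE do not recover within 6 months and 10% not even in 12 months". The next sentence adds: "Each year a GP refers about 2% of the patients with LE to an orthopaedic surgeon". Recruitment and enrollment places the trial among those referred patients: "All consecutive patients presenting to the department of orthopedic surgery with LE who meet the inclusion criteria".

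The primary endpoint is the change in provocation VAS 5 months after treatment (Primary outcome). Baseline descriptives are listed "regarding age, sex, body mass index, dominant arm, job and whether they smoke or not" (Demographic variables). Randomisation is stratified only by perceived work-relatedness, on the ground that pain reduction seems to depend on it (Randomization). Besides treatment and visit, the mixed model adjusts for "baseline pain VAS, the binary variable perceived aggravation of pain due to work" (Statistical analysis). Equivalence is accepted when the whole 98% confidence interval lies between −10 and +10 mm.

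**The concern.** The protocol accepts that a factor on which pain reduction depends should be balanced and modelled, and it does so for work-relatedness. Its own background figures suggest that time since onset is another such factor. A patient entering at the 6-week floor passes through most of the rapid-recovery period before the 5-month visit, while a patient entering after a year is in the persistent group. Both meet the criteria, and nothing in the stated analysis separates them.

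Two different things are at stake.

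- **Precision and chance imbalance.** A prognostic variable that sites must establish anyway, to check eligibility, is left unused.
- **Interpretation.** If the fluid acts mainly in patients who would not recover unaided, a large share of recent-onset patients makes the arms look more alike. The trial hypothesises no difference and has an equivalence rule, so a reader would want to know whether similarity held in long-standing cases too. The stated analysis could not show this.

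**Working it through.** **1. The plan's own sample size.** Sample size and power calculation gives 47 per arm, two-sided alpha 2% and a 10 mm difference, but no SD or power, so 47 cannot be reproduced. Solved backwards, SD = 10 × √(47/2) / (2.326 + 0.842) = 15.3 mm at 80% power (13.4 mm at 90%). No allowance for spontaneous recovery is stated.

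**2. Is duration likely to be prognostic?** Let S(t) be the share still symptomatic t months after onset. Background gives S(6) = 0.20 and S(12) = 0.10. Assume S(0) = 1, a constant rate within each half-year, and the later rate continuing after 12 months.

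- Months 0 to 6: ln(5)/6 = 0.268 per month.
- Months 6 to 12: ln(2)/6 = 0.116 per month.
- Ratio: about 2.3.

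The share still symptomatic 5 months after entry at e is S(e+5)/S(e):

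| Entry | Still symptomatic at 5 months | Recovered |
|---|---|---|
| 6 weeks (1.38 months) | 0.191/0.691 = 0.277 | 72% |
| 3 months | 0.355 | 65% |
| 6 or 12 months | 0.561 | 44% |

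**3. How firm is that?** Not very. The share still symptomatic at 6 weeks is not given. Letting it run from 20% to 100%, recovery after a 6-week entry runs from 1 − 0.191/0.20 = 4% to 1 − 0.191/1 = 81%. If referred patients recover at half the pace, S(t) becomes S(t/2): 51% persist for any entry up to 7 months, and 75% for entry at 12 months. Duration is then still prognostic, but only further out.

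**4. Chance imbalance.** Assume half the patients enter at about 6 weeks and half at 6 months or later, with a 45 mm VAS gap between recovered and unrecovered patients (neither figure is in the protocol). With 55 per arm:

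- SE of a difference in proportions = √(2 × 0.25/55) = 0.095.
- P(imbalance of at least 15 points) = P(|Z| > 0.15/0.095) ≈ 0.12.
- Shift = 0.15 × (0.561 − 0.277) × 45 ≈ 1.9 mm. It is 1.3 mm for a 30 mm gap and 2.6 mm for 60 mm.
- In the half-pace case with entry at 6 weeks versus 6 months, the shift is nil.

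**5. Precision.** On the same inputs:

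- Between-duration variance = 0.25 × (0.284 × 45)² ≈ 41.
- Overall persisting share = (0.277 + 0.561)/2 = 0.419, so recovery status alone gives variance 45² × 0.419 × 0.581 ≈ 493.
- Duration explains at most 41/493 = 8%, and adjustment narrows the interval by at most 1 − √0.917 ≈ 4%.

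**6. Possible dilution.** If a share r recovers to the same level in every arm and the fluid gives 10 mm in the others only, the mean difference is (1 − r) × 10. With SD 15.3 mm and 47 per arm:

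| r | Difference | Power |
|---|---|---|
| 20% | 8.0 mm | 58% |
| 44% | 5.6 mm | 29% |
| 72% | 2.8 mm | 7.5% |

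These rows illustrate the mechanism. The documents do not say which r applies.

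**The case against.** The strongest objection is that the 80% figure describes general-practice patients. The trial enrols from orthopaedic departments, to which about 2% are referred, and only after conservative treatment has failed. That stands: the rates cannot be carried over. It weakens the point without removing it, because the filter has no stated length and a patient just past 6 weeks can satisfy it.

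Randomisation balances duration in expectation, so leaving it out of the model does not itself draw the arms together. That stands fully.

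Dilution depends on recovered patients gaining nothing from the fluid. If the effect is the same in everyone, common recovery leaves the contrast unchanged apart from the floor at 0. That stands, so dilution is a possibility and not a finding.

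The Discussion remark that begins "Due to the self-limiting character in the majority of cases, the number of participants needed to demonstrate a clinically relevant difference" explains why not all injectables were included. It is not an admission that this comparison is compromised.

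The baseline list appears under a demographic heading in a condensed article, so it does not prove that duration goes unrecorded. The covariate list is explicit, however, and duration is not in it.

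**Conclusion.** The point holds as a modest, inexpensive improvement. Duration at entry is probably prognostic and is absent from the stated baseline list, strata and model. The demonstrable cost is small: at most about 4% of interval width, and about 1.9 mm in a 12% tail, under the assumed 45 mm gap, a half-and-half mix and the general-practice recovery curve. Dilution may be larger, but its size cannot be fixed from the documents.

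A reader might infer two stronger things, and neither is supported.

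- **That the design will produce a false finding of equivalence.** The whole 98% interval must lie within ±10 mm. At SD 15.3 mm and 47 per arm its half-width is 2.326 × 15.3 × √(2/47) = 7.3 mm, so the estimate must be within about 2.7 mm. It is therefore wrong to divide the 10 mm margin by the persisting share to obtain a hidden benefit. Moreover, a 45 mm gap with 28% unrecovered implies an SD of at least 45 × √(0.277 × 0.723) = 20.1 mm and a half-width of about 9.7 mm. An unadjusted 5-month comparison would then more likely be inconclusive than falsely equivalent.
- **That most enrolled patients will recover unaided.** Six weeks is a minimum, the actual mix of durations is not given, and the quoted recovery rates belong to a different population.

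**What to change.** 1. Record symptom duration at randomisation, where it is already established for eligibility. List it with the baseline variables and report it by arm.
2. Add it to the linear mixed model as a fixed covariate, for example as log months.
3. Report the 5-month pairwise contrasts by duration as a supportive analysis that does not decide the conclusion. It should not act as a gate: with half the patients (about 23 evaluable per arm) and SD 15.3 mm, the 98% half-width is 2.326 × 15.3 × √(2/23) = 10.5 mm, so the equivalence rule could not be met there.
4. Word any equivalence conclusion for lateral epicondylitis of more than 6 weeks that has not responded to conservative treatment, not for chronic disease without qualification.

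The cost is one case report form item, one model parameter and a supportive analysis that will be imprecise. Eligibility, treatment and sample size are unchanged.

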#### Exclusion criteria

Prior injection therapy (during this episode of LE), surgery or trauma at the affected elbow.Inflammatory diseases (i.e. rheumatoid arthritis, psoriatic arthritis, or reactive arthritis)Other elbow pathologyAdditional pain at the medial epicondyleNeck pain or shoulder pain correlated with elbow pain such as C6 radiculopathy or with disability of the arm or other chronic widespread pain syndromes.Traumatic onset of LEAbnormalities on the X-ray. Abnormal findings are defined as; all conditions that suggest other underlying pathology than LEAllergy for lidocaine

The inclusion of the patients will be done by an orthopedic surgeon or trained resident.

### Intervention

The patient will be randomized and included in one of the three treatment arms for lateral epicondylitis (Fig. 1):Perforation with application of autologous blood; a venous blood sample is injected in the affected tendon.Perforation with application of dextrose: solution with 5 ml 40% dextrose and 3 ml of 0.9% saline and 2 ml of 1% lidocaine.Perforation only, without application of a fluid.

**Fig. 1 Fig1:**
[figure not shown]
Flowchart study design

The percutaneous perforation will be performed by a single perforation at the affected elbow using the ITEC (Instant Tennis Elbow Cure) device (CE 621544, ITEC Medical B.V. Enschede, the Netherlands) (Fig. 2). This device is designed to perforate the Extensor Carpi Radialis Brevis (ECRB) tendon in an automated and standardized way. This device performs percutaneous, reproducible, accurate perforations with application of an exact amount of fluid ([name], [name], [name], [name], [name], [name]. Standardized ECRB perforations, unpublished). This is preceded by an ultrasound-guided localization of the affected ECRB tendon and depth measurement. The device perforates with a set of 12 sterile disposable needles (3 × 4), which are positioned according to anatomic landmarks of the elbow (Fig. 3). A brief instruction is required before using the device (ITEC Medical device user training). All physicians using the device are certificated.

**Fig. 2 Fig2:**
[figure not shown]
ITEC device (CE 621544, ITEC Medical B.V. Enschede, the Netherlands). Image under copyright by ITEC Medical B.V. and published with their permission

**Fig. 3 Fig3:**
[figure not shown]
ITEC disposable. Image under copyright by ITEC Medical B.V. (Enschede, the Netherlands) and published with their permission

The perforation of the affected tendon is as follows:Disinfection of the skin of the elbowPositioning of the arm in 90 degrees flexion in the elbow and 90 degrees abduction in the shoulder.Depth measurement of the Extensor Carpi Radialis Brevis tendon with an ultrasound probe (5–12 MHz phased array transducer).Setting the patient specific depth of the perforation on the device.Perforation by a single movement of the arm of the device in which the elbow is infiltrated with one of the injectables.Application of 12 drops of the injection fluid (if applicable), with a total amount of 0.4 cc (by a 2 cc syringe).

Before treatment a venous blood sample will be collected from each patient by a venipuncture from the unaffected arm. This sample is used for the treatment of patients in the autologous blood treatment arm and is covered by opaque tape. For the treatment with dextrose or perforation without infiltration this is redundant, but it will be done in order to ensure blinding. The venous blood sample is collected by a supporting nurse or by the physician who performs the treatment.

Co-interventions as visiting a physiotherapist, acupuncturist or osteopath are allowed and will be registered. The use of pain medication besides the needling therapy is allowed and will be registered. After the injection patients are advised to move their arm as they normally do but to avoid lifting and heavy labor for one week.

